**Methods:**

This is a hybrid type 3 effectiveness-implementation study that will include a multi-level, longitudinal, mixed-methods data collection approach designed to assess the sustained impact of a co-created multicomponent strategy relying on bidirectional learning, shared decision-making, and expertise by all team members. The study capitalizes on a combination of implementation strategies including mHealth outreach with culturally appropriate messaging, care coordination to increase engagement in high priority preventive services, and the co-design of these strategies using community advisory boards led by Community Weavers. Community Weavers are individuals with lived experience as members of an underserved community serving as cultural brokers between communities, public health systems, and researchers to co-create community-driven, culturally sensitive public health solutions. The study will use an adaptive implementation approach operationalized in a sequential multiple assignment randomized trial design of 300 participants from three sites in a Federally Qualified Health Center in Southern California. This design will allow examining the impact of various implementation strategy components and deliver more intensive support to those who benefit from it most. The primary effectiveness outcomes are COVID-19 vaccine completion, engagement in preventive services, and vaccine confidence. The primary implementation outcomes are reach, adoption, implementation, and maintenance of the multicomponent strategy over a 12-month follow-up period. Mixed-effects logistic regression models will be used to examine program impacts and will be triangulated with qualitative data from participants and implementers.

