The multicomponent strategy is an adaptive approach that utilizes tailored mHealth messaging and care coordination to increase COVID-19 vaccine uptake. The SMART assignment arms are described in Table 2. The trial will span 4 years inclusive of 3 years of active implementation and 1 year of sustainment/maintenance. As outlined in Fig. 2, both randomization and analysis will be conducted at the individual participant level. At enrollment, participants will be stratified by current COVID-19 vaccination status and status of other preventive services vis-à-vis a risk score and then randomized into the first-stage intervention (mHealth outreach or standard of care). Response or lack of response after the completion of the first stage intervention will determine if participants continue in their initial first-stage intervention or re-randomized to increased intensity intervention. Nonresponders in the standard of care arm will be equally re-randomized into either mHealth outreach or care coordination for stage 2. Nonresponders in mHealth outreach will be re-randomized into mHealth or mHealth plus care coordination for stage 2. Nonresponse will be defined as not being up to date on COVID-19 vaccination OR having at least one outstanding preventive service need.

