	COVID-19 vaccine uptake	Up-to-date vaccine record defined as completed vaccine series and required boosters as recommended by Centers for Disease Control guidelines for COVID-19 vaccination at the time of implementation to be confirmed through electronic health records
	Preventive services engagement	Up-to-date age- and gender-specific preventive services (e.g., mammograms, adult immunizations, blood pressure screenings, A1c screenings, colorectal cancer screenings). Standards will be defined for each participant based on their demographic and health characteristics

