### Analytic approach

Quantitative data from surveys, study databases, and EHRs will be summarized using simple descriptive statistics along with data visualization methods to understand patterns and characteristics of responders and nonresponders and to guide adaptive implementation. Parametric and nonparametric tests will be employed to compare the survey responses between the arms of the trial variables and clinic locations. Factors will initially be assessed at the univariate level and then used to build multivariable models to assess independent associations of multiple factors on vaccination uptake, including community level factors such as prevalence of COVID-19 vaccination, history of COVID-19 infection, and primary community language group. Multinomial logistic regression models will explore the relation between standard of care, mHealth outreach, and mHealth plus care coordination and COVID-19 vaccine uptake, while controlling for a variety of demographic and socioeconomic variables and comorbidities, as well as FQHC clinic characteristics. Additionally, the association between adaptive interventions and the secondary clinical composite outcome, preventive services engagement, including age and gender-specific services will be evaluated. Descriptive analysis will be used to characterize within subgroup differences. Mixed-effects logistic regression models will be used to identify factors associated with COVID-19 vaccine uptake and vaccine confidence using EHR and demographic data collected with participant evaluation surveys.

Qualitative data will be culled from interviews, periodic reflections, and study databases. All qualitative data will be coded using a rapid qualitative data analytic approach guided by the domains of PRISM, informed by prior work of the lead and senior authors across diverse contexts [58, 72, 73]. This approach involves developing a templated matrix of summary responses from interviews, followed by coding by a qualitative analytic team based on pre-defined themes while allowing for new sub-themes to emerge [74]. Group coding for consensus building, team-based review of codes, and double coding to verify acceptable inter-rater reliability will occur throughout the coding process. Community Weavers and clinic partners will be invited to review the coded data to support sense-making and develop action items based on the data.

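### The stated model for vaccine uptake compares three treatment labels that stage-1 response helps to form; they match neither the stage-1 arms nor the four embedded strategies, and they omit care coordination alone

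*Protocol article*

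**What the plan says.** All references are to the protocol article.

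- **Methods, Design.** Participants are first randomised to mHealth outreach or standard of care. Stage-1 response "will determine if participants continue in their initial first-stage intervention or re-randomized to increased intensity intervention". For the first arm: "Nonresponders in the standard of care arm will be equally re-randomized into either mHealth outreach or care coordination for stage 2". For the second: "Nonresponders in mHealth outreach will be re-randomized into mHealth or mHealth plus care coordination for stage 2". The response rule is: "Nonresponse will be defined as not being up to date on COVID-19 vaccination OR having at least one outstanding preventive service need".
- **Measures, Table 4.** Vaccine uptake is an "Up-to-date vaccine record defined as completed vaccine series and required boosters" under the guidelines in force at the time.
- **Power calculations.** Vaccine completion is the primary effectiveness outcome. The trial is sized for a SMART with a binary outcome: success 0.70 for adaptive interventions, 0.45 for standard of care, equal re-randomisation of nonresponders, at least 252 participants, 300 enrolled.
- **Analytic approach.** "Multinomial logistic regression models will explore the relation between standard of care, mHealth outreach, and mHealth plus care coordination and COVID-19 vaccine uptake", adjusted for demographic, socioeconomic, comorbidity and clinic variables. The next sentence but no other speaks of adaptive interventions, and it concerns the secondary outcome. Mixed-effects logistic models appear here only as a way to find factors associated with uptake and confidence.
- **Abstract, Methods.** "Mixed-effects logistic regression models will be used to examine program impacts".

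**The concern.** In a SMART, randomisation supports comparisons of the first-stage arms, of the second-stage options among nonresponders to a given arm, and of the embedded strategies. Here there are four strategies: start on standard of care and give nonresponders mHealth; start on standard of care and give nonresponders care coordination; start on mHealth and continue it; start on mHealth and add care coordination.

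The three labels in the uptake model correspond to none of these sets. Because being up to date on the vaccine is part of the response rule, the labels are also partly determined by an earlier value of the outcome. At stake is a result that makes the programme's most intensive arm look worse than standard of care when it does nothing, or that hides a real benefit. One randomised second-stage group would also contribute nothing to the uptake comparison.

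**Working it through.** **1. Who carries each label at the end (from Design).**

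| Label | Stage-1 responders | Stage-1 nonresponders |
|---|---|---|
| Standard of care | from standard of care | none: all are moved |
| mHealth | from mHealth | half from each first-stage arm |
| mHealth plus care coordination | none | half of those from mHealth |
| Care coordination alone (not listed) | none | half of those from standard of care |

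The halves from standard of care follow from the stated equal re-randomisation. Power calculations assumes the same for nonresponders generally.

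**2. The plan's own sample size.** With two-sided 5% (sidedness assumed), 80% power and 0.45 versus 0.70, the log-odds-ratio formula is n = (1.960 + 0.842)² × [1/(0.45×0.55) + 1/(0.70×0.30)] / (ln OR)².

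- ln OR = ln(0.70/0.30) − ln(0.45/0.55) = 1.048.
- n = 7.849 × 8.802 / 1.098 = 62.9.
- For two embedded strategies with different first stages, total = 2n(2 − r), where r is the stage-1 response rate. At the conservative r = 0 this is 4 × 62.9 = 251.6, so 252.
- 252/0.85 = 296.5, so 297, and 300 is enough.

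The figure is reproduced, and it is reproduced by a comparison of embedded strategies.

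**3. Expected uptake with no effect of any component.** Assumptions not in the article: 1:1 at stage 1; a share s of up-to-date participants with no outstanding service; a retention rate for up-to-date status; a conversion rate for the rest.

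*First illustration:* 45% up to date at entry, 10% of the rest vaccinated in each stage, 90% retention in the second stage, s = 0.5.
- Up to date after stage 1: 0.45 + 0.55×0.10 = 0.505. Responders: 0.505×0.5 = 0.2525. Nonresponders: 0.7475.
- Share of nonresponders already up to date: 0.2525/0.7475 = 0.338.
- Standard of care (responders only): 90%.
- mHealth plus care coordination (nonresponders only): 0.338×0.90 + 0.662×0.10 = 37%.
- mHealth: (0.126×0.90 + 0.374×0.370)/0.5 = 50%.
- Everyone: 0.505×0.90 + 0.495×0.10 = 50%, which is the true value for every strategy.

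*Second illustration:* 45% up to date after stage 1, retention 0.8, conversion 0.2, s = 0.5.
- Responders 0.225, nonresponders 0.775, of whom 0.225/0.775 = 0.290 are up to date.
- Standard of care 80%. mHealth plus care coordination: 0.290×0.8 + 0.710×0.2 = 37%. mHealth: (0.1125×0.8 + 0.3875×0.374)/0.5 = 47%.

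**4. Range under the null.** Simulation with N = 255, 3,000 trials per row and 45% up to date after stage 1. The test is an unadjusted three-group chi-square at 5%, standing in for the model.

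| s | Retention | Conversion | Uptake: standard of care / mHealth / mHealth plus care coordination | Rejections |
|---|---|---|---|---|
| 0.5 | 1.0 | 0.2 | 100/56/43% | 100% |
| 0.5 | 0.8 | 0.2 | 80/47/37% | 95% |
| 0.5 | 0.6 | 0.3 | 60/43/39% | 36% |
| 0.25 | 0.8 | 0.2 | 80/47/43% | 65% |
| 1 | 0.45 | 0.45 | 45/45/45% | 4% |

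In the last row stage-1 status carries no information about final status, and the bias vanishes. In the four rows above it, the gap between standard of care and the most intensive arm runs from 60 − 39 = 21 to 100 − 43 = 57 points.

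**5. The same data analysed by strategy.** Relative weights are 1 for responders and 2 for re-randomised nonresponders. In the second illustration each strategy has mean 0.225×0.8 + 0.775×0.374 = 47%, the true value. Comparing standard of care then mHealth with mHealth then mHealth plus care coordination rejected in 5.4 to 6.1% of null trials in every scenario run.

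**6. The omitted group.** Its share is one quarter of the nonresponder fraction: 0.7475/4 = 19% in the first illustration; (1 − 0.45×0.25)/4 = 22% at s = 0.25; 0.495/4 = 12% at the limit where no up-to-date participant has an outstanding service.

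**7. Can the covariates repair it?** Stage-1 response is not among them. Adding it would not identify the comparison, because no nonresponder remains on standard of care and no responder receives mHealth plus care coordination. Stratification at enrolment does not help, since the selection happens after stage 1.

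**The case against.** The strongest reply is that the article never says how participants are assigned to the three labels or that the regression is unweighted, and a condensed article may leave weighting and coding to an analysis plan. That is fair on technique, but it does not rescue the sentence. No coding turns three labels into two first-stage arms or four strategies, and one randomised option is missing from the list.

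Several stronger readings are tempting and are not supported:

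- *That this is the designated main analysis.* The article says the models explore the relation, names no model as primary, and in the Abstract gives programme impacts to mixed-effects logistic regression. What can be said is that it is the only stated model relating the named treatments to uptake.
- *That the groups were never randomised against each other.* Standard of care versus mHealth is randomised at stage 1, and mHealth versus mHealth plus care coordination among mHealth nonresponders. The three-group comparison as a whole is not.
- *That standard of care would look best whatever the true effect.* Only null effects were simulated. With s = 0.5, retention 0.6 and conversion 0.3, an intensive arm that vaccinated more than (0.60 − 0.290×0.6)/0.710 = 60% of its participants not yet up to date would pass standard of care.
- *That the gap is as wide as 90% versus 10%.* That needs response judged on the vaccine alone, which is not the rule in Design.
- *That a multinomial model is itself wrong.* With two categories it is ordinary logistic regression.

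The part of the bias between mHealth and mHealth plus care coordination can also be small: 47% versus 43% at s = 0.25.

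**Conclusion.** The point stands as a fault in what is stated. Read as a comparison by treatment received, the uptake model is biased towards standard of care and against the most intensive arm whenever up-to-date status at stage 1 predicts final status. That direction follows from the Design section alone. The size does not: 90/50/37% and 80/47/37% under no effect are illustrations resting on assumed retention, conversion and outstanding-service rates and on 1:1 first-stage allocation, none of which the article gives.

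The model also does not match the sample-size basis, which concerns adaptive interventions in a SMART, although Power calculations names no pair of strategies. A reader might infer that the sample size is wrong too. It is not: 252 reproduces.

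**What to change.** Replace the sentence in Analytic approach with a comparison of the four embedded adaptive interventions on vaccine uptake, with everyone analysed as randomised:

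- Use weighted-and-replicated logistic regression with robust standard errors by participant. Each stage-1 responder is replicated into both strategies consistent with the first-stage arm.
- Set weights to the inverse of the actual randomisation probabilities. Responders to nonresponders is 1:2 under equal re-randomisation, or 2 and 4 if the first stage is 1:1. State the first-stage ratio.
- Name one primary contrast between two strategies with different first stages, tested at the 5% level. One candidate is mHealth with care coordination added on nonresponse versus standard of care with mHealth on nonresponse; other pairs are defensible.
- Include care coordination alone.
- Keep any comparison by treatment received as descriptive.
- Make the Abstract and Analytic approach name the same model for programme impact.

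The cost is protocol and analysis-plan wording plus standard SMART code. No extra data or participants are needed.

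### The adjustment classes stated for the arm comparison do not include the factors that stratify randomisation, and the separate association models ask for more community-level coefficients than three clinics support if those factors are assigned by clinic

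*Protocol article*

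**What the plan says.** Methods, Design, describes the first randomisation: "participants will be stratified by current COVID-19 vaccination status and status of other preventive services vis-à-vis a risk score". It adds that "both randomization and analysis will be conducted at the individual participant level". Table 4 defines the uptake outcome as an up-to-date vaccination record, so the first stratification factor is in substance the outcome measured at baseline.

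Methods, Analytic approach, then describes two different kinds of model.

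- **Factor-association models.** "Factors will initially be assessed at the univariate level and then used to build multivariable models", with the aim of independent associations with uptake, "including community level factors such as prevalence of COVID-19 vaccination, history of COVID-19 infection, and primary community language group".
- **Arm-comparison model.** A multinomial logistic regression relates standard of care, mHealth, and mHealth plus care coordination to uptake, "while controlling for a variety of demographic and socioeconomic variables and comorbidities, as well as FQHC clinic characteristics".

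There are three clinics with 100 participants each (Participants). The Setting section gives each clinic one main preferred language: Vietnamese, Arabic and Spanish. Table 1 shows one community vaccination rate and one positivity rate per clinic, under a label saying that the data are by zip code.

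**The concern.** Two separate matters are at stake.

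First, the design balances the arms on vaccination status and preventive-service status, but the classes of covariate named for the arm comparison do not include them. A person's earlier vaccination status is very likely to predict later status. Stratified randomisation makes the arms more alike on that factor than chance would. A model that ignores the factor does not credit this balance, so its standard error is too large for the design and power is lost.

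Second, anything measured only at clinic level can take three values in this trial. That leaves two contrasts between clinics, however many community variables are listed. If several are entered together as clinic-level values, software will drop some or return arbitrary coefficients, and the independent associations that the article promises cannot be delivered.

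**Working it through.** **The plan's own figure.** Inputs from Power calculations: success 0.70 against 0.45, 5% type I error, 80% power, equal re-randomisation of nonresponders. Taking a two-sided test, the log-odds-ratio formula for two embedded regimens is

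N = (1.96 + 0.8416)² × [2r + 4(1 − r)] × [1/(p1·q1) + 1/(p0·q0)] / (ln OR)².

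With r = 0 (no first-stage responders, the conservative choice):

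- (1.96 + 0.8416)² = 7.849, times 4 = 31.40
- 1/(0.70 × 0.30) + 1/(0.45 × 0.55) = 4.762 + 4.040 = 8.802
- OR = (0.70/0.30)/(0.45/0.55) = 2.852; ln OR = 1.048; squared = 1.098
- N = 31.40 × 8.802/1.098 ≈ 251.6, so 252

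The stated 252 is reproduced, and this point does not change it.

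**Cost of ignoring the stratification factors.** Two arms, N = 252, 1:1 allocation within strata, binary logistic model with and without the two factors, 3,000 simulated trials per setting. Assumptions: 45% vaccinated at baseline (the article's current rate), 50% at high risk, no second stage, marginal uptake 0.45 against 0.60. The smaller difference was used because a simple two-arm comparison of 0.45 with 0.70 needs only 61 per arm for 80% power; with 126 per arm both analyses would sit near the ceiling.

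| Assumed log OR: vaccination, risk | Power without | Power with | Difference (points) | Type I error without |
|---|---|---|---|---|
| 0, 0 | 67.0% | 67.1% | 0.1 | 5.1% |
| 1, 0.5 | 67.7% | 70.3% | 2.6 | 4.2% |
| 2, 0.5 | 70.8% | 77.5% | 6.7 | 2.3% |
| 3, 1 | 71.1% | 85.3% | 14.2 | 1.0% |

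With the factors included, type I error stayed between 4.5% and 5.1%. The Monte Carlo standard error for power is about √(0.7 × 0.3/3000) = 0.8 points.

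**Rank of the community-level terms.** Table 1 gives vaccination 807, 745 and 803 per 1,000 and positivity 22,589, 24,530 and 23,427 per 100,000. Any column that is constant within clinic lies in a space of dimension 3, including the intercept.

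| Columns entered | Columns | Rank |
|---|---|---|
| Intercept, vaccination rate, positivity, language (2), all by clinic | 5 | 3 |
| The same plus two clinic indicators | 7 | 3 |
| Intercept, vaccination rate and language (2) by clinic; infection history per person | 5 | 4 |
| Intercept, vaccination rate by clinic; infection history and language (3 terms) per person | 6 | 6 |
| Intercept, rates by zip code (two or more per clinic, assumed values), language (2) by clinic | 5 | 5 |

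In the first row, 5 − 3 = 2 coefficients are not estimable. Adding the arm indicator to that design raises the rank by one, so the arm effect remains estimable.

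**The case against.** The strongest reply is that this is a condensed article. Its covariate list is open and worded by class; it excludes nothing, and the final set may be fixed in an analysis plan that is not shown. That stands, so the point is that the stated classes do not include the stratification factors, not that the trial has decided to omit them. The stratification sentence can also be read as one combined score; the argument is the same for one factor or two.

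A reader might infer several stronger things that the documents do not support.

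- **That community factors replace the stratification factors.** They appear in the association models. The arm-comparison sentence mentions only clinic characteristics.
- **That univariate screening selects the arm-comparison covariates.** That step also belongs to the association models, and no selection rule is given.
- **That the community coefficients are certainly not estimable.** This requires one value per clinic. The Table 1 label refers to zip codes, language varies within clinics (clinic 1 has 32% Vietnamese and 7% Spanish), and values by zip code or by person can restore full rank.
- **That adjustment is worth 20% to 57% more participants.** This follows from 1/(1 − R²) with R² of 0.17 to 0.36. It rests on assumed final uptake of 85–90% against 30–45% by baseline status, figures that are not in the article, and on a linear-model formula when the planned models are logistic. Because up-to-date status follows the guidance in force, people up to date at baseline may also lapse.
- **That clinic must be a stratification factor at both randomisations.** No defect shown here calls for it.

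**Conclusion.** The point holds in two parts of limited size.

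First, if the arm-comparison model is run with only the classes stated, it ignores the factors on which participants were randomised. The test is then conservative and loses about 0 to 14 power points at N = 252. Where in that range the trial falls depends on prognostic strength, which the article does not give, and on the simulation's simplification to two arms and one stage. There is no added risk of a false positive.

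Second, the independent community-level associations cannot all be estimated if the factors are assigned by clinic: two of the four community coefficients are lost. The article does not say at which level they will be assigned. The randomised arm effect is untouched in every case. The change is worth making because it recovers power at almost no cost and removes a promise that three clinics may be unable to keep.

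**What to change.** In every arm-comparison outcome model, include baseline vaccination status, the preventive-service risk-score stratum and clinic as two indicators. The clinic indicators take the place of separate clinic characteristics, since they already use both between-clinic degrees of freedom.

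In the association models, use each participant's own language and infection history, or define the community factors by participant zip code. Report any community figure available only by clinic descriptively.

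This is a change of analysis wording. The stratification factors and clinic are known at randomisation; individual language and infection history, or zip code, need to be confirmed as available from the health record or survey. The only thing given up is a set of between-clinic associations that three clinics cannot provide.
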